### Program Assessment and Translation

The BIFI manual has undergone several stages of thorough forward and backward translation, content review, and revision by a panel of local experts. The expert panel included 2 clinical psychologists, 1 certified translator (psychology content translator), and 2 rehabilitation physicians. All the panels had experience with working in the related fields for >5 years.

On the basis of the experts’ feedback and comments, a few changes were made to the module. The first change was the use of a more simple Malay language. The second change was related to the pictures used in the material. The experts suggested changing to universal pictures, so that they can be adapted locally.

The final product of the manual was revised to match the local population and to ensure the intervention’s fidelity.

### Pilot Study

A pilot study was conducted to assess the feasibility of the BIFI program among caregivers of patients with TBI in Malaysia. In total, 10 caregivers of patients with TBI participated, and only 8 (80%) managed to complete all 5 sessions. A caregiver withdrew owing to work commitments and another withdrew owing to personal issues. Challenges included (1) punctuality of the participants, (2) duration of the sessions, and (3) homework material.

Overall, participants were satisfied with the content and delivery of the program. Some suggested to increase the duration of the sessions and to reduce the amount of homework given. All feedback was taken into consideration, and slight alterations were performed to accommodate the participants and the program.

### Intervention

BIFI will be the main intervention tool. It is a structured intervention module specifically for patients with TBI and their caregivers, developed by [name] [name] and colleagues from Virginia Commonwealth University, United States. This module is based on CBT [44] and FST [53].

This module consists of several objectives: (1) providing patients and caregivers with fundamental information about brain injury, (2) helping caregivers to better understand the effects of brain injury, (3) teaching patients and caregivers about problem-solving skills, (4) teaching coping strategies, (5) recognizing progress and personal strengths and helping them to access community and professional resources, and (6) teaching effective communication skills.

BIFI was designed to be implemented in 5 sessions, with 90 to 120 minutes for each session. In total, 2 or 3 topics will be covered in each session. Using a standardized and family-focused intervention, BIFI was found to be beneficial for caregivers of patients with TBI both immediately and at 3 months after the intervention [31,54,55]. Furthermore, another study also showed that patients with TBI and caregivers reported high ratings of helpfulness, goal attainment, and satisfaction regarding the BIFI program [55].

Several measures will be taken to ensure that all participants comply with the intervention program. The program would also be conducted during weekends to accommodate the schedule of caregivers of patients with TBI. They are also allowed to choose any day during weekends at their convenience. However, they are required to complete all 5 sessions within the stipulated time frame.

### Control Group

The control group or treatment-as-usual group will not receive any additional treatment during the study period. Participants in the control group will receive the usual treatment at their respective hospitals. According to the Malaysian Clinical Practice Guidelines for early management of head injury, all patients who have been discharged are recommended to attend follow-up sessions at the hospital [56]. It is recommended that patients with moderate and severe head injuries are scheduled for routine clinic follow-up. However, patients with a mild head injury can be followed up via clinic visits or telephone calls. Apart from the routine follow-up, other programs tailored for patients with TBI and their caregivers are also considered as treatment as usual in this RCT. For example, the Acquired Brain Injury Rehabilitation Unit in HRC would offer a program known as “Return to Work” for suitable patients and caregivers. A similar program is also available in HSB.

### Outcomes

#### Overview

The outcomes of this study will be assessed using self-report questionnaires at four periods: (1) baseline, (2) 5 weeks (after the treatment), (3) 3-month follow-up, and (4) 6-month follow-up. The schedule of enrollment, interventions, and assessments are presented in Table 1.

**Table 1 table1:** Schedule of enrollment, interventions, and assessments.

				Study period										
				Enrollment		Allocation		After allocation				Follow-up		
Time point				–t_1_		0		Baseline t_1_		5-week intervention t_2_		3 months t_3_		6 months t_4_
**Enrollment**														
		Eligibility screen	✓											
		Informed consent	✓											
		Randomization	✓											
		Allocation			✓									
**Interventions**														
	BIFI^a^ and TAU^b^													
	TAU only													
**Assessments**														
	Sociodemographic data				✓									
	BDI^c^						✓		✓		✓		✓	
	PANAS^d^						✓		✓		✓		✓	
	CSI^e^						✓		✓		✓		✓	
	FNQ^f^						✓		✓		✓		✓	

^a^BIFI: Brain Injury Family Intervention.

^b^TAU: treatment as usual.

^c^BDI: Beck Depression Inventory.

^d^PANAS: Positive and Negative Affect Schedule.

^e^CSI: Caregiver Strain Index.

^f^FNQ: Family Needs Questionnaire.

#### Primary Outcomes

The primary outcome for this study is the TBI caregiver’s emotional distress, which will be measured using two scales: (1) BDI and (2) Positive and Negative Affect Schedule (PANAS). The measures are described in the Methods section.

#### Secondary Outcomes

The secondary outcomes will include (1) burden (CSI), (2) life satisfaction (SWLS), and (3) caregiver’s needs (FNQ). The measures are described in the Methods section.

### Data Collection and Time Frame

Recruitment for potential participants was conducted by the rehabilitation physicians at both hospitals, who are also the coinvestigators of the study. They screened for potential participants among the caregivers of patients with TBI who attend regular rehabilitation therapy and follow-up at their clinics. These caregivers were then invited to participate in this study. If the caregiver was interested in learning more about the study, they were led to another room, where the investigator explained the study in great detail and answered any questions that the caregivers had. At this stage, a patient information sheet about the nature of the study was provided to the potential participants.

The investigator then left the room for 10 to 15 minutes to allow the caregiver to read the information and to think about whether they would like to participate in the study. If they expressed interest in participating, they were asked to sign the consent form before completing the questionnaire. The same questionnaire used at baseline will be distributed immediately after the intervention, at 3-month follow-up, and at 6-month follow-up. The questionnaire will take approximately 30 to 40 minutes to complete. Data collection was performed between December 2018 and December 2020.

### Measures

#### BDI Questionnaire

The original version of BDI is a self-reporting questionnaire consisting of 21 items on a 4-point scale. It is assessed using a Likert scale ranging from 0 (symptom not present) to 3 (symptom very intense). The total score can range from 0 to 63. BDI is used to measure the main symptoms of depression such as mood, pessimism, sense of failure, self-dissatisfaction, guilt, punishment, self-dislike, self-accusation, suicidal ideas, crying, irritability, social withdrawal, indecisiveness, body image change, work difficulty, insomnia, fatigability, loss of appetite, weight loss, somatic preoccupation, and loss of libido [57]. Respondents who scored between 0 and 9 are considered negative for depression. In contrast, those who score >9 are screened positive for depression, whereby a score between 10 and 18 indicates mild to moderate depression, score between 19 and 29 indicates moderate to severe depression, and score between 30 and 63 indicates severe depression (60). The BDI test is widely used globally, and its content, concurrent, and construct validity have been tested. High concurrent validity ratings are detected between BDI and other depression instruments such as the Minnesota Multiphasic Personality Inventory and the Hamilton Depression Scale. Correlation rating of 0.77 was obtained between the inventory and psychiatric ratings. BDI also showed high construct validity with the medical symptoms it measures. The study by Beck and Steer [58] reported a coefficient α rating of 0.92 for patients at outpatient clinics and 0.93 for college students. BDI has been translated into the Malay language and validated for use among the Malaysian population. Internal consistency (Cronbach α) ranged from 0.71 to 0.91, and the validity of BDI-Malay was deemed as satisfactory [59].

#### PANAS Questionnaire

PANAS comprises 2 mood scales that measure the positive affect (PA) and negative affect (NA), respectively. PANAS is used to assess the relationship between positive and negative effects on personality traits. Each of the PA and NA scales consists of 10 items that define their meanings. Respondents need to answer 20 items on a 5-point scale that ranges from 1 (very slightly or not at all) to 5 (extremely). The total score generated will range between 10 and 50, with low scores indicating low (positive or negative) affect and high scores indicating high (positive or negative) affect. The reliability and validity of PANAS were moderately good [60]. For the PA scale, the Cronbach α coefficient was between 0.86 and 0.90, and for the NA scale, it was between 0.84 and 0.87. Over 8 weeks, the test-retest correlations were between 0.47 and 0.68 for PA and between 0.39 and 0.71 for NA. PANAS also had strong validity with other measures of general distress and dysfunction, depression, and anxiety [61]. The Malay-translated version of PANAS had Cronbach α coefficient of 0.73 [62].

#### CSI Questionnaire

CSI is a self-rated, 13-item questionnaire that measures strain related to care provision. It consists of 5 major domains related to employment, financial, social, time, and physical aspects. The items can be answered as yes (score=1) or no (score=0). The maximum score for the questionnaire is 13. A score >7 is categorized as “having strain,” whereas a score <7 is defined as “no strain.” There is no age limit for the individuals who could be assessed with the tool**.** CSI has been translated into the Malay language, and the Cronbach α coefficient for the 13-item CSI-Malay was 0.79, indicating good internal consistency reliability of the scale [63].

#### SWLS Questionnaire

SWLS evaluates the respondents’ agreement with 5 statements on overall satisfaction with life (eg, in most ways, my life is close to my ideal). It uses a 7-point Likert scale ranging from 1 (strongly disagree) to 5 (strongly agree), giving rise to a range of scores between 5 and 35. A score of 20 is considered the neutral point of the scale. Scores between 5 and 9 indicate that the respondent is extremely dissatisfied with life. In contrast, scores between 31 and 35 show that the respondent is extremely satisfied. SWLS is reported as having excellent internal consistency (Cronbach α=0.88) and good test-retest reliability (*r*=0.68). SWLS has been translated into the Malay language and validated among the Malaysian population [64,65]. The Malay SWLS has been found to have good internal consistency (Cronbach α=0.83).

#### FNQ Questionnaire

FNQ is a self-administered questionnaire consisting of 37 items. It was designed to determine the family needs of patients with TBI. The family members will rate the importance of each need on a scale ranging from 1 (not important) to 4 (very important). FNQ is divided into 6 areas, namely, health information, emotional support, instrumental support, professional support, community support network, and involvement with care. It has been proven to have good content and construct validity and good internal consistency Spearman-Brown split-half reliability at 0.75 [66].

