**Objective:**

This study aims to assess the effectiveness of BIFI in reducing emotional distress and burden of care, fulfilling the needs, and increasing the life satisfaction of caregivers of patients with TBI at government hospitals in Malaysia.

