### Aims of This Study

This study aims to assess the effectiveness of BIFI in reducing emotional distress and burden of care, besides fulfilling the needs and increasing the life satisfaction of caregivers of patients with TBI in selected hospitals.

The hypotheses of this study are as follows:

There is a significant association between the sociodemographic and clinical characteristics of patients with TBI and the emotional distress, burden of care, needs, and life satisfaction of caregivers of patients with TBI.There is a significant difference in the mean scores of caregivers’ emotional distress, burden of care, needs, and life satisfaction between the intervention and control groups before the intervention, after the intervention, at 3-month follow-up, and at 6-month follow-up.The sociodemographic and clinical characteristics of the patients are predictors of the intervention outcomes.

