### Statistical Analysis

Data analysis will be performed using SPSS software (version 24.0; IBM Corp). Descriptive statistics will be used to describe the characteristics of participants. Continuous data will be reported as means and SDs or as medians and IQRs. Categorical data will be reported as percentages and frequencies. The comparison of the means between the 2 groups will be performed using a paired samples 2-tailed *t* test. In addition, 1-way ANOVA and repeated measure ANOVA will be conducted to identify any significant differences in mean scores of emotional distress (BDI), caregiver’s needs (Family Needs Questionnaire [FNQ]), burden of care (Caregiver Strain Index [CSI]), and life satisfaction (Satisfaction With Life Scale [SWLS]) before the intervention, after the intervention, at 3-month follow-up, and at 6-month follow-up between the intervention and control groups. Multivariate regression analysis will be used to determine the predictors of intervention outcomes.

The intention-to-treat analysis will be performed accordingly. Assumptions of normality and homogeneity of variance will be conducted and adjusted where necessary.

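### As described, the FNQ records how important each need is, not whether it is met, so a difference in mean FNQ scores cannot by itself show that BIFI fulfils caregivers' needs

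*Protocol article*

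**What the plan says.** **The aim.** The abstract's Objective lists, after distress and burden, "fulfilling the needs, and increasing the life satisfaction of caregivers of patients with TBI at government hospitals in Malaysia". Aims of This Study repeats it: "besides fulfilling the needs and increasing the life satisfaction of caregivers of patients with TBI in selected hospitals". Anticipated Findings, in the Discussion, frames the evaluation in the same way.

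**The hypothesis.** The same Aims section predicts a difference without a direction: "There is a significant difference in the mean scores of caregivers’ emotional distress, burden of care, needs, and life satisfaction", between the two arms across the assessment times.

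**The outcome.** Needs are tied to one instrument: "The secondary outcomes will include (1) burden (CSI), (2) life satisfaction (SWLS), and (3) caregiver’s needs (FNQ").

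**The analysis.** Statistical Analysis lists "caregiver’s needs (Family Needs Questionnaire [FNQ"]) among the scores whose means are compared between arms by one-way and repeated measures ANOVA at the four assessments.

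**The instrument.** The FNQ Questionnaire section states: "FNQ is a self-administered questionnaire consisting of 37 items". It then gives the response format: "The family members will rate the importance of each need on a scale ranging from 1 (not important) to 4 (very important"). It names six areas of need and reports validity and reliability. It gives no second response, no scoring rule and no statement of what a higher or lower score means.

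**The concern.** Importance and fulfilment are different quantities. Importance is how much a caregiver values having a need addressed. Fulfilment is whether it has been addressed. The aim concerns the second, and the scale described measures the first.

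Two features make this more than loose wording. First, the hypothesis has no direction and the FNQ section gives none, so a significant difference either way could be presented as support for the aim. Second, the content of BIFI overlaps with the areas that the FNQ covers. The Intervention section lists basic information about brain injury and help in reaching community and professional resources. The FNQ areas include health information, professional support and the community support network. It is plausible, though the article does not show it, that teaching on these subjects changes how important they seem, independently of whether the need is met.

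At stake is one of four stated effects. A shift in importance ratings could be published as evidence that BIFI meets caregivers' needs.

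**Working it through.** The plan gives no figure for the FNQ, so there is nothing to reproduce. The check compares the sections and then asks what the described score can detect.

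**Sections side by side**

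| Element | Where stated | Content |
|---|---|---|
| Aim | Abstract, Objective; Aims of This Study; Anticipated Findings | Fulfil caregivers' needs |
| Hypothesis | Aims of This Study | Difference in mean needs score, no direction |
| Outcome | Secondary Outcomes | Needs, by FNQ only |
| Analysis | Statistical Analysis | Mean FNQ scores compared between arms |
| Response scale | FNQ Questionnaire | Importance of each need, 1 to 4 |
| Timing | Study Procedure | Same questionnaire at T1, T2, T3 and T4 |

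The chain from hypothesis to outcome, analysis and scale holds together as a comparison of importance. It does not connect to the aim.

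**What the score can detect**

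1. Inputs from the FNQ section: 37 items, each scored 1 to 4 for importance.
2. Take the extreme case. Every caregiver in both arms rates every need 4. In the BIFI arm all 37 needs are met, and in the control arm none is.
3. Mean item score: 4 in each arm, so the difference is 4 − 4 = 0.
4. Area scores: every item in every area is 4 in both arms, so each area difference is also 0.
5. Summed total, which is an assumption because the article gives no scoring rule: the range would be 37 × 1 = 37 to 37 × 4 = 148. Both arms score 148, and the difference is 148 − 148 = 0.
6. Now reverse it. If fulfilment is the same in both arms but importance ratings differ, the FNQ difference is not zero although no additional need has been met.

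The result does not depend on how the items are combined. The score moves with importance and carries no term for fulfilment.

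**Comparison with the other instruments**

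The Measures section says how the other scores are to be read: depression bands for the BDI, low and high affect for PANAS, a strain cut-off for the CSI, and dissatisfied to satisfied for the SWLS. The FNQ has no such statement, so its direction of benefit cannot be inferred.

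**The case against.** The strongest reply is that this is a condensed article. The FNQ section is one paragraph introducing a published instrument, and scoring is the kind of detail a full protocol carries. Nothing in the article says that importance was the only response collected. This stands in part. The full protocol may hold a met or unmet rating, and a reader might infer that the trial has no valid outcome for needs or cannot answer this aim at all. The article does not support that stronger reading, because it does not show everything that was collected. But the point is not about an omitted detail. The article states the aim, the comparison and the response scale, and these do not fit together. If a met rating exists, the FNQ description is incomplete in a way that misdescribes the outcome.

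A second reply is that the hypothesis, the secondary outcome and the analysis refer only to needs, and that the abstract's conclusion anticipates better psychological well-being without mentioning fulfilment. This is correct, and it confines the mismatch to the aim. The aim is nevertheless stated three times, including in the Discussion.

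A third reply is that the article reports good content and construct validity for the FNQ. That also stands. The point does not question the instrument. Validity for assessing family needs does not turn an importance rating into a measure of fulfilment.

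**Conclusion.** The point holds for the FNQ as the article describes it. A between-arm difference in mean FNQ scores cannot by itself support a conclusion that BIFI fulfils caregivers' needs, and no direction of benefit is given. In the extreme case, complete fulfilment in one arm and none in the other give a difference of 0 under summed, averaged or area scoring.

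The conclusion assumes that the scores analysed are built from the importance ratings, the only responses described. It does not rest on the 37 to 148 total.

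Its reach is limited. The FNQ is one of three secondary outcomes. The primary outcome of emotional distress is unaffected, as is the sample size, which is based on the BDI.

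**What to change.** Which correction applies depends on what was collected.

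- **If a met, partly met or not met rating was collected:** correct the FNQ description to say so. Make the extent to which needs are met the FNQ outcome, analyse it with the trial's own longitudinal between-group comparison, and state which direction is a benefit.
- **If only importance was collected:** restate the aim and hypothesis as perceived importance of needs, and do not conclude that BIFI fulfils needs.

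Adding a response to the questionnaire is no longer an option: the Data Collection and Time Frame section ends collection in December 2020, and the Results section puts analysis at its final stage. The first option costs re-scoring of data already held. The second costs a change of wording and a narrower secondary claim. Either should be settled before the results are published.

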### Study Procedure

All the screening procedures to identify the participants based on inclusion and exclusion criteria were performed before the intervention program by rehabilitation physicians in the respective hospitals. The recruitment started in November 2018 and was continued until the required sample size was achieved. The BIFI program will be conducted in the Malay or English language depending on the needs of the caregivers. The participants in the intervention group will be divided into smaller groups of 10 people each. Each group will receive a scheduled time and date to attend the program at the hospital. The program will be conducted by the principal investigator, who is also a clinical psychologist. The clinical psychologist must at least have 5 years of experience.

At the baseline of the program (T1), all participants are required to complete the questionnaires (BDI, CSI, PANAS, FNQ, and SWLS). The same questionnaire will be distributed immediately after the intervention program (T2), at 3-month follow-up (T3), and at 6-month follow-up (T4). The average time needed to complete the questionnaire is 30 to 40 minutes. The follow-up sessions (T3 and T4) will be scheduled by the coinvestigators. The session will be conducted at the respective hospitals by the coinvestigators to prevent any bias during follow-up. The participants were also encouraged not to share the intervention materials with other caregivers until data collection is completed.

The intervention group will undergo the BIFI program. The BIFI program will be scheduled for 5 sessions as recommended by the developer of the module. Each session will take approximately 90 to 120 minutes. The participants are required to attend all 5 sessions. A total of 5 weeks is needed for each group to complete the program, and 2 groups will be scheduled every week. All the sessions will start with an overview of the topic and end with the summary and homework assignments. Participants will be required to complete the homework given according to the module. This homework will then be reviewed by the principal investigator in the subsequent session.

For the control group that receives the usual standard treatment, the caregivers will need to complete the questionnaires at similar time points as the intervention group.

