### Ethical Considerations

#### Approval

This study has been reviewed by the Medical Research and Ethics Committee Malaysia, Ministry of Health Malaysia (NMRR 18-2253-42951). Ethics approval has been obtained from the National Medical Research Register (NMRR-18-2253-42951-IIR) for the study to be conducted at the Ministry of Health settings. Please refer to Multimedia Appendices 1 and 2 for further details of Research Ethics comments and review. The approval letter was received on December 19, 2018. The recruitment period started in December 2018 and was completed on December 18, 2020.

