## Results

The participant recruitment process began in January 2019 and was completed in December 2020. A total of 100 participants were enrolled in this study, of whom 70 (70%) caregivers are women and 30 (30%) are men. We are currently at the final stage of data analysis. The result of this study is expected to be published in 2024.

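### Recruitment has three stated start dates, one before the ethics letter arrived, and recruitment and data collection both close in December 2020, which does not fit a 6-month visit for everyone

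*Protocol article*

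**What the plan says.** **Start of recruitment.** The protocol article gives three dates.

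- Study Procedure: "The recruitment started in November 2018 and was continued until the required sample size was achieved".
- Approval (under Ethical Considerations): "The recruitment period started in December 2018 and was completed on December 18, 2020".
- Results, and the Abstract in the same words: "The participant recruitment process began in January 2019 and was completed in December 2020".

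**Ethics letter.** Approval also states: "The approval letter was received on December 19, 2018". The date on which approval was granted is not given.

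**Data window.** Data Collection and Time Frame ends with: "Data collection was performed between December 2018 and December 2020". Shortly before, the same paragraph lists the assessments concerned: "The same questionnaire used at baseline will be distributed immediately after the intervention, at 3-month follow-up, and at 6-month follow-up".

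**Follow-up schedule.** The Outcomes overview and Study Procedure set four assessments: baseline (T1), after the 5-week programme (T2), 3 months (T3) and 6 months (T4). The control group is assessed at similar times. On programme length, Study Procedure says: "A total of 5 weeks is needed for each group to complete the program, and 2 groups will be scheduled every week".

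**The concern.** At most one of the three start dates can be right. The earliest falls before the ethics letter was received, so it raises the question of whether anyone consented before approval. The latest, January 2019, also conflicts with data collection beginning in December 2018, because the baseline questionnaire is completed only after recruitment and consent.

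The closing dates raise a different problem. A trial that enrols until 18 December 2020 and needs a 6-month visit from each participant must collect data into mid-2021. The stated data window stops in December 2020.

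The 6-month time point matters to the analysis. The second hypothesis names it, and Statistical Analysis plans a repeated measures ANOVA over all four time points. In its usual form that method drops any participant who lacks one of them. If the dates are right as printed, late entrants leave that analysis because of the calendar, before any ordinary dropout.

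**Working it through.** The article gives no figure to reproduce for the dates. The check is calendar arithmetic on its stated dates.

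**1. Start dates against the letter (19 December 2018)**

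- November 2018: 1 November is 48 days before and 30 November is 19 days before. Every day in the month precedes receipt.
- December 2018: before or after receipt, depending on a day that is not given.
- January 2019: after receipt, but later than the stated start of data collection.

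**2. The last possible entrant (18 December 2020)**

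- T2 = entry + 35 days = 22 January 2021.
- T3 = 18 March 2021 (3 months from baseline) or 22 April 2021 (3 months from programme end).
- T4 = 18 June 2021 or 22 July 2021 on the same two anchors.

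All of these fall after the stated close.

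**3. Last entry date that still allows T4 inside the window**

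Formula: close − 6 months if T4 counts from baseline, or close − 6 months − 35 days if it counts from programme end. The article fixes neither the anchor nor the closing day, so both are varied.

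| Data close | T4 from baseline | T4 from programme end |
|---|---|---|
| 18 Dec 2020 | 18 June 2020 | 14 May 2020 |
| 31 Dec 2020 | 30 June 2020 | 26 May 2020 |

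Counting 6 months as 183 days moves the second row to 1 July and 27 May.

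**4. Share of the recruitment period after those dates**

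Formula: days from the cut-off to 18 December 2020 ÷ days from recruitment start to 18 December 2020. The start is taken as 1 November 2018 (778 days), 19 December 2018 (730 days) or 1 January 2019 (717 days).

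- Smallest: 30 June to 18 December 2020 = 171 days; 171/778 = 22.0%.
- Largest: 14 May to 18 December 2020 = 218 days; 218/717 = 30.4%.

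For T3 the cut-offs run from 14 August to 30 September 2020. The shares run from 79/778 = 10.2% to 126/717 = 17.6%. For T2 the cut-offs are 13 and 26 November 2020.

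**5. What that would mean for numbers, under even accrual only**

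- With 22 to 30 of 100 participants unable to reach T4, 70 to 78 remain, or about 35 to 39 per arm if the loss is equal between arms.
- Sample Size Estimation gives SD 9.355, difference 5.86, and z values 1.96 and 0.845. Taking the difference squared in the denominator: 2 × (1.96 + 0.845)² × 9.355² / 5.86² = 40.1 per arm. Adding 25% gives 40.1 × 1.25 = 50.1, which matches the planned 50.
- The calendar alone could therefore use up roughly the whole 25% dropout allowance at 6 months.

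**The case against.** The strongest reply is that these are drafting slips in an article that mixes past and future tense.

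- **The two closing dates do not contradict each other.** Recruitment can end on 18 December 2020 and data collection can end that month; late entrants would then lack T3 and T4. This stands. The conflict is with complete 6-month follow-up.
- **The recruitment end date may mean something else.** It falls one day short of two years after the letter was received, so it could mark the end of a study period. Study Procedure gives a stopping rule, reaching the required sample size, with no date. Either would remove the T4 problem, but the article says neither, and at least one printed date would then need correcting.
- **November 2018 may refer to screening.** The sentence follows one on screening, and Data Collection and Time Frame treats screening and invitation as steps before consent. A reader might infer that participants were enrolled without approval. The documents do not support that: they give no consent dates, and they give the date the letter was received, not the date approval was granted.
- **The percentages rest on even accrual.** This also stands. No entry dates are given, and Limitations reports that the programme stopped for several months and that participants were hesitant to attend. The true share could be near zero or well above 30%.
- **Handling of missing data usually belongs in an analysis plan.** That is fair in general, but the article itself names repeated measures ANOVA. Advice on a model that keeps partial follow-up is relevant only if the window did close in December 2020.

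**Conclusion.** The start-date contradiction is certain: three dates are printed, and the November one precedes receipt of the ethics letter. It is also certain that a December 2020 close for both recruitment and data collection cannot be squared with a 6-month assessment for every participant. One of the closing dates is wrong, or follow-up is incomplete by design of the calendar.

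The consequence is conditional. If December 2020 was both the last enrolment and the last assessment, entrants after a cut-off between 14 May and 1 July 2020 could not have T4. Even accrual would put that at about 22% to 30% of participants, with 10% to 18% also lacking T3.

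A reader might go further and infer that 6-month data do not exist for late entrants, or that the 6-month comparison rests on early recruits only. The documents do not establish either. Even on the even-accrual figures, some 70% to 78% of participants could reach T4.

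The point should be corrected because it bears on ethics compliance and on who enters the repeated measures analysis. The records that settle it should already be held.

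**What to change.** 1. Reconcile the Abstract, Data Collection and Time Frame, Study Procedure, Approval and Results against signed consent forms and visit records. State one recruitment start, the date of last enrolment and the date of the last T4 assessment.
2. State the date approval was granted, and report whether anyone consented before it. If so, refer this to the ethics committee for direction on those data.
3. If assessments continued into 2021, correct the data-collection window. Nothing further is then needed on the 6-month analysis from this point.
4. If data collection did close in December 2020, report the number per arm able to reach T3 and T4. Replace the repeated measures ANOVA with a likelihood-based mixed model that keeps participants with partial follow-up.

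The cost is a check of existing records and some rewording. Under step 4 there is also a change of model, and the stated usable number at 6 months may be smaller.
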